### Explanatory analysis via multivariate model

A multivariate model of variables independently associated with death will include: age, enrolment GCS, TBM diagnostic category (definite, probable, possible), study drug allocation (dexamethasone vs. placebo), CD4 count, CSF total leucocytes, CSF total neutrophils, CSF blood:glucose ratio, CSF lactate. Numeric variables will be analysed using restricted cubic splines. We will not include any interactions.

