## Baseline characteristics

Definition: The following baseline characteristics will be summarised by treatment arm for ITT and PP analyses: age, sex, country, site, diagnostic category (definite, probable, possible, or not TBM by Marais criteria
^
10
^), history of previous tuberculosis treatment, chest X-ray findings (no TB/miliary TB/pulmonary TB), enrolment MRC TBM grade, enrolment Glasgow coma score (GCS), weight (kg), duration of symptoms, cranial nerve palsy, hemiplegia, para/tetraplegia, urinary retention, history of diabetes, HbA1c, history of intravenous drug use, hepatitis B sAg positivity, hepatitis C Ab positivity, alanine aminotransferase (ALT), bilirubin, full blood count (haemoglobin, white cell count, platelets), plasma sodium,
*leukotriene A4 hydrolase* (
*LTA4H*) genotype (CC/CT/TT), routine CSF parameters (opening pressure, total leucocytes, total neutrophils, total lymphocytes, protein, blood:CSF glucose ratio, Ziehl-Neelsen stain, Gene Xpert MTB/RIF, Gene Xpert MTB/RIF Ultra, mycobacterial culture), duration of anti-tuberculosis chemotherapy (days) before enrolment, enrolment anti-TB regimen, anti-TB drug susceptibility results in culture-confirmed sub-group (multi-drug resistant [MDR] TB or rifampicin mono-resistant TB, isoniazid resistant non-MDR, pre-extensively drug resistant [XDR] TB, XDR TB, no or other resistance), HIV infection (new or known diagnosis), anti-retroviral therapy (ART) treatment at enrolment (ART naïve, ≤3 months of ART, >3 months of ART) and time to starting ART (if ART naïve), enrolment CD4 count (median values and categories [<50, 51–100, 101–200, >200]), HIV viral load. These will be described in a baseline variable table (
Table 2).

**Table 2. T2:** Baseline characteristics template table.

Characteristic	Dexamethasone (N=XX)		Placebo (N=XX)	
	N	Summary statistic	N	Summary statistic
Age (years)	XX	XX (XX,XX)	XX	XX (XX,XX)
Sex - male	XX	XX (XX%)	XX	XX (XX%)
Country	XX	XX (XX%)	XX	XX (XX%)
Site - HTD - PNT - Cipto Mangunkusumo - Persahabatan	XX XX XX XX	XX (XX%) XX (XX%) XX (XX%) XX (XX%)	XX XX XX XX	XX (XX%) XX (XX%) XX (XX%) XX (XX%)
Diagnostic category - Definite TBM - Probable TBM - Possible TBM - Not TBM	XX XX XX XX	XX (XX%) XX (XX%) XX (XX%) XX (XX%)	XX XX XX XX	XX (XX%) XX (XX%) XX (XX%) XX (XX%)
Previous tuberculosis treatment	XX	XX (XX%)	XX	XX (XX%)

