Chest X-ray findings - No tuberculosis - Miliary tuberculosis - Pulmonary tuberculosis	XX XX XX	XX (XX%) XX (XX%) XX (XX%)	XX XX XX	XX (XX%) XX (XX%) XX (XX%)
Modified MRC grade - Grade I - Grade II - Grade III	XX XX XX	XX (XX%) XX (XX%) XX (XX%)	XX XX XX	XX (XX%) XX (XX%) XX (XX%)
Glasgow coma score	XX	XX (XX,XX)	XX	XX (XX,XX)
Weight (kg)	XX	XX (XX,XX)	XX	XX (XX,XX)
Duration of symptoms (days)	XX	XX (XX,XX)	XX	XX (XX,XX)
Neurological signs - Cranial nerve palsy - Hemiplegia - Paraplegia/tetraplegia - Urinary retention	XX XX XX XX	XX (XX%) XX (XX%) XX (XX%) XX (XX%)	XX XX XX XX	XX (XX%) XX (XX%) XX (XX%) XX (XX%)
History of diabetes	XX	XX (XX%)	XX	XX (XX%)
HbA1c (%)	XX	XX (XX,XX)	XX	XX (XX,XX)
History of intravenous drug use	XX	XX (XX%)	XX	XX (XX%)
Hepatitis B sAg positivity,	XX	XX (XX%)	XX	XX (XX%)
Hepatitis C Ab positivity	XX	XX (XX%)	XX	XX (XX%)
Alanine aminotransferase (ALT) (IU/L)	XX	XX (XX,XX)	XX	XX (XX,XX)
Bilirubin (µmol/L)	XX	XX (XX,XX)	XX	XX (XX,XX)
Full blood count - Haemoglobin (g/dL) - White cell count (x10 ^3^/ µL) - Platelets (x10 ^3^/ µL)	XX XX XX	XX (XX,XX) XX (XX,XX) XX (XX,XX)	XX XX XX	XX (XX,XX) XX (XX,XX) XX (XX,XX)
Plasma sodium (mmol/L)				
*Leukotriene A4 hydrolase* - TT - CT - CC	XX XX XX	XX (XX%) XX (XX%) XX (XX%)	XX XX XX	XX (XX%) XX (XX%) XX (XX%)
CSF parameters - Opening pressure (cmH _2_0) - Total leucocytes (cells/mm ^3^) - Total neutrophils (cells/mm ^3^) - Total lymphocytes (cells/mm ^3^) - Protein (g/L) - Blood:CSF glucose	XX XX XX XX XX XX	XX (XX,XX) XX (XX,XX) XX (XX,XX) XX (XX,XX) XX (XX,XX) XX (XX,XX)	XX XX XX XX XX XX	XX (XX,XX) XX (XX,XX) XX (XX,XX) XX (XX,XX) XX (XX,XX) XX (XX,XX)
CSF microbiological tests - Positive ZN stain - Positive GeneXpert MTB/RIF - Positive GeneXpert MTB/RIF Ultra - Positive mycobacterial culture	XX XX XX XX	XX (XX%) XX (XX%) XX (XX%) XX (XX%)	XX XX XX XX	XX (XX%) XX (XX%) XX (XX%) XX (XX%)
Duration of anti-tuberculosis chemotherapy before enrolment (days)	XX	XX (XX,XX)	XX	XX (XX,XX)
Enrolment anti-tuberculosis chemotherapy regimen - Rifampicin - Isoniazid - Pyrazinamide - Ethambutol - Streptomycin	XX XX XX XX XX	XX (XX%) XX (XX%) XX (XX%) XX (XX%) XX (XX%)	XX XX XX XX XX	XX (XX%) XX (XX%) XX (XX%) XX (XX%) XX (XX%)
Anti-tuberculosis drug resistance * - Multi-drug resistant or rifampicin mono-resistant - Isoniazid resistant non-MDR - Pre-XDR - XDR - No or other resistance	XX XX XX XX XX	XX (XX%) XX (XX%) XX (XX%) XX (XX%) XX (XX%)	XX XX XX XX XX	XX (XX%) XX (XX%) XX (XX%) XX (XX%) XX (XX%)

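### The explanatory model enters CSF total leucocytes beside their own neutrophil component, so the leucocyte row mainly reflects lymphocytes and the neutrophil row a difference between two effects

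*SAP article*

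**What the plan says.** The section Explanatory analysis via multivariate model opens with "A multivariate model of variables independently associated with death will include" and then lists the covariates. Among them is the pair "CSF total leucocytes, CSF total neutrophils", within the run "CD4 count, CSF total leucocytes, CSF total neutrophils, CSF blood:glucose ratio, CSF lactate". On functional form it says "Numeric variables will be analysed using restricted cubic splines", and it adds "We will not include any interactions", so the terms are additive.

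The Baseline characteristics section lists the CSF counts as "total leucocytes, total neutrophils, total lymphocytes". Table 2 gives all three in the same absolute unit, cells per mm³. Neutrophils are therefore an additive part of the total, and the lymphocyte count is collected but not entered in the model.

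The section does not say how the neutrophil term is to be read when the total is also in the model. It also gives no knots, scale, model type or significance rule for the covariates.

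**The concern.** The stated purpose of this model is to identify variables independently associated with death, so its product is the set of covariate rows and how readers interpret them. When a whole and one of its parts are both entered, holding the whole fixed means that more of the part is less of the remainder. The row labelled neutrophils then does not describe having more neutrophils with everything else unchanged, and the row labelled leucocytes no longer describes the total count.

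A published table could therefore show neutrophils as a predictor when only lymphocytes carry prognostic information. It could also show neutrophils as irrelevant when both cell types matter equally.

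**Working it through.** The SAP states no figure on this point, so there is nothing to reproduce. The check has an algebraic part, which needs no assumed effect size, and a simulation part, which does.

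**1. Algebra.** Let T be total leucocytes, L lymphocytes and N neutrophils, with T ≈ L + N (other white cells ignored). Let bL and bN be the log hazard ratios per unit. Then

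bL·L + bN·N = bL·(T − N) + bN·N = bL·T + (bN − bL)·N.

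In linear form the planned pair is a reparametrisation of lymphocytes plus neutrophils. The coefficient of T is bL, and the coefficient of N is bN − bL.

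**2. Numerical check of the identity.** Cox fits with linear terms on 20,000 simulated patients:

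| True (bL, bN) | Expected N term, planned pair (bN − bL) | Fitted T, N (planned pair) | Fitted L, N (separate counts) |
|---|---|---|---|
| (−0.3, 0) | +0.3 | −0.309, +0.308 | −0.309, −0.001 |
| (−0.3, −0.3) | 0 | −0.291, +0.005 | −0.291, −0.286 |
| (−0.3, +0.2) | +0.5 | −0.308, +0.501 | −0.308, +0.193 |

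The neutrophil term can thus show an effect where neutrophils have none of their own, hide a real one, or enlarge one.

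**3. With splines, at the trial's size.**
- *From the SAP:* 520 patients (Structure and status of trial) and mortality approaching 50% (Background). The simulation gave about 240 deaths, and 240/520 = 46%.
- *Assumed:* a Cox model containing the two cell counts only; four knots; log-normal lymphocytes (median 80, log-SD 1.2) and neutrophils (median 20, log-SD 1.5); log-scale correlation 0 to 0.6; lymphocyte log hazard ratio −0.4 per SD (hazard ratio exp(−0.4) = 0.67); no neutrophil effect.

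The table gives the share of trials in which a likelihood-ratio test of the neutrophil spline reached p < 0.05. There were 150 runs per row, and 300 in the row marked *.

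| Hazard depends on | Spline scale | Correlation | Planned pair | Neutrophils + lymphocytes | Planned pair: neutrophil contrast opposite in sign to the lymphocyte effect |
|---|---|---|---|---|---|
| log lymphocytes | raw | 0.3 | 37% | 7% | 93% |
| log lymphocytes | log | 0.3 | 33% | 5% | 81% |
| log lymphocytes | raw | 0.6 | 18% | 8% | 86% |
| log lymphocytes | log | 0.6 | 20% | 7% | 74% |
| log lymphocytes | log | 0 | 63% | 9% | 91% |
| raw lymphocytes* | raw | 0.3 | 31% | 6% | 64% |
| raw lymphocytes | log | 0.3 | 19% | 4% | 54% |
| neither cell type | raw | 0.3 | 5% | 3% | – |
| neither cell type | log | 0.3 | 5% | 5% | – |

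The sign column compares the 25th with the 75th percentile of neutrophils. With 150 runs, the Monte Carlo standard error is about 4 points near 35% and 2 points near 5%.

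**4. Different assumed distributions.** Here total leucocytes are log-normal (median 100, log-SD 1.2), the mean neutrophil share is 30%, about 45% die, and only lymphocytes act.
- Lymphocyte hazard ratio 0.7 per SD, 400 runs: neutrophils reach p < 0.05 in 19-24% of trials with the planned pair, against 5-7% with separate counts.
- Hazard ratio 0.6, 400 runs: 34-35% against 5%.
- Smaller repeats: 20-21% (hazard ratio 0.7) and 29% (0.6) against 7-9% with 100 runs; 17-26% against 2-7% with 150 runs.

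**5. Total plus neutrophil percentage.** On the assumptions of step 4, this alternative reached p < 0.05 in 20-21% (hazard ratio 0.7) and 39-40% (0.6) with 100 runs, and in 20-43% with 150 runs. That is as often as the planned pair, or more often. At a fixed total, a higher percentage is the same exchange of lymphocytes for neutrophils.

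**The case against.** The best defence is that the neutrophil term is not false. In a multivariable model, an independent association ordinarily means an association given the other listed covariates, and total leucocytes is one of them. If only lymphocytes matter, a patient with more neutrophils at the same total has fewer lymphocytes and a truly different hazard. On this view the simulated percentages are power to detect a real conditional contrast and not a type I error rate. This stands, and it is why the point concerns which question the row answers and not whether the fit is valid. It does not remove the point, because the SAP nowhere says that the row is a contrast at fixed total, and a reader of a table of predictors will take it to be about neutrophils.

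A reader might also infer that a lymphocyte effect must reappear on neutrophils with the opposite sign. The documents do not support that. Exact reversal belongs to linear terms, whereas the SAP plans splines, under which the opposite sign appeared in anything from 54% to 93% of simulated trials.

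Nor does the point reach the trial's conclusions. In linear form the fit and the study-drug coefficient are the same under either parametrisation. The primary Cox model has treatment as its only covariate, and the explanatory model is not among the eight secondary endpoints.

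Finally, the cell distributions, the correlation, the lymphocyte effect and the p < 0.05 criterion are not in the SAP. That is correct, and the sizes are illustrations for that reason. The algebra needs none of them.

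**Conclusion.** The point holds as a minor flaw of specification. Pairing total leucocytes with neutrophils serves the model's stated aim poorly, because one row mainly reflects lymphocytes and the other reflects a difference between two effects.

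Under assumed distributions and a lymphocyte hazard ratio of 0.6 to 0.7 per SD, neutrophils without an effect of their own reached p < 0.05 in about 17-35% of simulated trials in most settings. The extreme was 63%, when the two counts were taken as uncorrelated on the log scale. Separate counts gave roughly 2-9%. A neutrophil effect equal to the lymphocyte effect can disappear from the neutrophil row.

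The conclusion rests on two conditions: the total is close to lymphocytes plus neutrophils (any other white cells would share the place given here to lymphocytes), and lymphocytes are prognostic. With no effect of either cell type, the planned pair stays at about 5%.

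**What to change.** In Explanatory analysis via multivariate model, replace the pair "CSF total leucocytes, CSF total neutrophils" with CSF total neutrophils and CSF total lymphocytes, each as a restricted cubic spline. Each row then refers to the cell type it names.

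The cost is one line of SAP wording. Both counts are already collected and tabulated, and the number of model terms does not change. The small downside is that the total leucocyte count no longer has its own row.

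Total leucocytes plus neutrophil percentage should not be offered as an equivalent, because it keeps the same contrast at fixed total. If the sponsor prefers the present pair, the section should at least say that the neutrophil term is read at a fixed total leucocyte count.

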## Data availability

No data is associated with this article.
